### Methods in analysis to handle protocol non-adherence and any statistical methods to handle missing data {20c}

In case more than 10% of the patients in the intervention arm do not undergo the [^18^F]FET PET scan, an additional per-protocol analysis will be performed. This traditional per-protocol analysis will be supplemented by an instrumental variable analysis in which the complier average causal effect (CACE) will be estimated for the subpopulation of patients undergoing the extra [^18^F]FET PET scan. For the primary outcome measure of unnecessary interventions, no, or minimal missing data are expected, as data are all available in the electronic patient files. Dedicated study-specific data acquisition is performed by study personnel. Due to the organization of Dutch healthcare, loss to follow-up of patients is minimal. However, in the event that missing data do occur, imputation will not be applied to the primary outcome measure; (multiple) imputation is not considered to be optimally reliable or appropriate due to the nature of this outcome and its limited predictability. The occurrence of unnecessary treatments is highly dependent on contextual factors, such as physician decision-making and the clinical course of the illness, which makes accurate imputation difficult and potentially misleading. Therefore, for this specific outcome, an available-case analysis will be conducted including only those participants with available primary outcome data—expected to be all, or virtually all randomized patients. Where appropriate, sensitivity analyses will be performed to evaluate the robustness of the findings.

Regarding the HRQOL outcomes, standards of the field will be followed by using methods that are robust to missing data, e.g., linear mixed modeling combined with single-timepoint analyses.

### Plans to give access to the full protocol, participant-level data and statistical code {31c}

The full protocol and statistical code will be available upon request once the report has been published.

Participant-level data concerning baseline characteristics and major clinical outcomes will be made available as supplemental document of the article. Other participant-level data may be provided to non-commercial researchers upon reasonable request.

## Oversight and monitoring

### Composition of the coordinating center and trial steering committee {5d}

The main team of the coordinating center consists of two principle investigators and one coordinating researcher, who meet on a weekly basis to discuss day-to-day issues but also the implementation and management of the trial. The two principle investigators, the trial agency of the division and the project controller form the basis of the steering committee. They monitor the trial progress and provide oversight. The principle investigators of the local centers coordinate the execution of the trial in their center and together with the steering committee they form the study group. An unaffiliated physician is accessible for independent patient support. In addition, a datamanager is involved in overseeing data collection, storage, analysis, and quality control processes within the research project.

The monitoring of the study in all centers will be performed by the trial agency of the sponsor.

### Composition of the data monitoring committee, its role and reporting structure {21a}

As [^18^F]FET PET is a well-established, safe imaging method in glioma patients and is recommended as an optional imaging modality for these patients in Dutch and international guidelines, the risk of participation in this trial is considered negligible. Due to this negligible risk, establishing a data monitoring committee is not needed, according to the NFU (Nederlandse Federatie van Universitaire Medische Centra) guidelines [32].

### Adverse event reporting and harms {22}

All possibly/probably related adverse events (AEs) reported spontaneously by the subject or observed by the investigator or his staff will be recorded. These possibly/probably related AEs will be reported for 30 days in both groups. All serious adverse events (SAEs) will be systematically reported for 7 days in both groups, regardless of relatedness. Both time windows start from the date of the PET scan in the intervention group and 7 days after randomization in the control group. The risk of (S)AEs caused by the additional [^18^F]FET PET scan is considered to be negligible. However, due to the poor life expectancy of glioblastoma patients, expected SAEs are hospitalization, persistent or significant disability or incapacity, or death due to glioblastoma progression. All AEs and SAEs meeting the aforementioned criteria will be included in trial publications. CTCAE 5.0 terminology will be used for classification [33].

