## Introduction

### Background and rationale {6a}

Glioblastomas are incurable progressive brain tumors with a variable, but poor prognosis. After surgery, chemoradiation with concomitant and adjuvant temozolomide chemotherapy offers effective, albeit temporary, palliation for many patients, with median overall survival of 14–16 months [1, 2]. In the months following radiotherapy, ~ 50% of patients will develop changes on MRI, suggestive of recurrence. In a majority of these patients, these MRI changes are classified as pseudoprogression [3]. Pseudoprogression is defined as treatment-induced increasing, or new, contrast enhancement which is mostly self-limiting and requires a different management strategy than tumor recurrence. Pseudoprogression will be used in this paper as an encompassing term that includes radionecrosis and other treatment-related effects after (chemo-)radiotherapy. Discrimination between pseudoprogression and tumor progression on MRI can be notoriously challenging [4]. In the patients that are eventually diagnosed with pseudoprogression, initial diagnostic uncertainty is common, which may lead to an increased risk of misdiagnoses and unnecessary interventions [5, 6].

Currently, in the Netherlands, in these patients with diagnostic uncertainty on MRI, the multidisciplinary team prefers to wait for a next scan in 6–12 weeks’ time for definitive diagnosis, leading to potential delay of diagnosis and adequate management and causing psychological burden for patients and their relatives with impact on quality of life [7].

The use of positron emission tomography (PET) with the radioligand [^18^F]Fluoro-ethyl-tyrosine, or [^18^F]FET PET in short, has the potential to differentiate treatment-related changes from tumor recurrence with higher accuracy compared to current clinical standard MRI including perfusion-weighted MRI [8–10]. Meta-analyses of literature confirm that addition of [^18^F]FET PET to MRI has higher diagnostic accuracy for differentiation of pseudoprogression from tumor recurrence compared with MRI alone [11, 12]. Recent literature has led to evidence-based recommendations by the Response Assessment in Neuro-Oncology (RANO) working group to add [^18^F]FET PET imaging to MRI in cases with diagnostic uncertainty [13].

However, this advice is not based on prospective randomized patient benefit- or cost-effectiveness studies, as neither have been performed.

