### Objectives {7}

#### Primary objectives

To determine, in glioblastoma patients with diagnostic uncertainty between pseudoprogression and tumor progression on a follow-up MRI after concomitant chemoradiation (“index MRI”), whether the clinical management guided by an additional [^18^F]FET PET scan leads to fewer unnecessary interventions and better health-related quality of life after 12 weeks, compared with management based on MRI only.

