### Intervention description {11a}

Patients in the investigational arm will undergo the extra [^18^F]FET PET scan, with use of the O-(2-^18^F-fluoroethyl)-L-tyrosine ([^18^F] FET) tracer. The tracer will be provided free of charge by Curium™ for a subset of the patients (based on logistical availability and scheduling per patient). For this study, Curium™ does not have a role in the design, execution, analysis, interpretation, manuscript writing and/or decision to publish.

[^18^F]FET PET scanning will be performed according to the joint European Association of Nuclear Medicine (EANM)/European Association of Neurooncology (EANO)/Response Assessment in Neurooncology (RANO) guideline [20]. In most patients, a static scan (20–40 min post-injection) will be performed. Patients will be asked for additional (opt-in) consent to undergo a dynamic [^18^F]FET PET scan. If the logistics of the research site allow for this scan, these patients will undergo dynamic scanning (continuous scanning 0–40 min post-injection). Interpretation will be done by a nuclear medicine physician from the local center according to current European guidelines [20]. Central review will be performed by a panel of nuclear medicine physicians from the study team, specialized in [^18^F] FET PET scans.

Patients are treated according to current standard-of-care that is determined by the treating physician/multidisciplinary team, but will be based on the diagnosis from the static [^18^F]FET PET findings:In case of [^18^F]FET PET-diagnosis of tumor recurrence: a change in treatment regime will be made. Redo-debulking will be done only for clinical indications, including mass reduction or cytoreduction.In case of [^18^F]FET PET-diagnosis of pseudoprogression, or equivocal results: the ongoing treatment or observation will be continued, with addition of steroids and/or bevacizumab if needed for symptom relief. Redo-debulking will only be done for the rare indication of refractory symptoms of mass effect due to pseudoprogression.

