#### Other study parameters

Patient characteristics: sex, age.Oncological characteristics: date of diagnosis of initial tumor, O^6^-methylguanine DNA methyltransferase (MGMT) promotor methylation status, CDKN2A/B-status, Karnofsky performance score at baseline and during clinical examination moments.Questionnaires EORTC-QLQ-C30 + BN20, EQ-5D, iPCQ and iMCQ at baseline, measured between informed consent and randomization.Diagnostic- and treatment characteristics: surgical- and concomitant chemoradiation characteristics, usage of bevacizumab, dosage of dexamethasone, follow-up scans, blood tests.Final diagnosis during follow-up after study intervention: tumor recurrence or pseudoprogression.Notes from multidisciplinary meetings, describing diagnostic uncertainty and initial management after diagnostic imaging.

The schedule of assessments is illustrated in Table 1.

**Table 1 Tab1:** Schedule of assessments

Visit	Index MRI result	Informed consent	Randomization	FET PET^a^	FET PET result^a^				
Study time	Day 1	± Days 3–14	±Days 5–16	± Days 7–30	± Days 10–33	Week 6	Week 12	Month 6	End of trial
Unnecessary interventions								X	
EORTC-QLQ-C30 + BN20/EQ-5D/iPCQ/iMCQ		X				X	X	X	
Karnofsky performance score	X				X^a^				
Final diagnosis								X	
Survival status								X	X^b^
Healthcare consumption								X	
Adverse events^c^				X	X				

^a^The intervention group only

^b^A survival sweep will be performed at the end of the trial

^c^All possibly/probably related adverse events will be reported for 30 days in both groups. All serious adverse events will be reported for 7 days in both groups

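### Serious adverse events are collected regardless of relatedness only until about 4 days after the PET result, so non-fatal serious harms of the management that follows are largely not recorded as harms in either arm

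*Protocol article*

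**What the plan says.** The section on adverse event reporting and harms {22} sets two windows. For serious events: "All serious adverse events (SAEs) will be systematically reported for 7 days in both groups, regardless of relatedness". For other events: "These possibly/probably related AEs will be reported for 30 days in both groups". The latter are events that the subject reports spontaneously or that staff observe. On timing: "Both time windows start from the date of the PET scan in the intervention group and 7 days after randomization in the control group". The section adds that events meeting these criteria will be reported in the trial publications. Footnote c to Table 1 repeats the windows: "All possibly/probably related adverse events will be reported for 30 days in both groups. All serious adverse events will be reported for 7 days in" (the footnote closes by naming the two arms).

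The primary objective is to determine "whether the clinical management guided by an additional [^18^F]FET PET scan leads to fewer unnecessary interventions and better health-related quality of life after 12 weeks". The intervention description {11a} ties treatment to the PET reading; for example: "In case of [^18^F]FET PET-diagnosis of tumor recurrence: a change in treatment regime will be made". For pseudoprogression or an equivocal reading, the ongoing treatment or observation continues. Co-primary outcome 1 is judged after 6 months of follow-up.

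The section on the data monitoring committee {21a} calls the risk of taking part in the trial negligible because the scan is safe, and concludes: "Due to this negligible risk, establishing a data monitoring committee is not needed". The section on post-trial care {30} argues in the same way. Section {22} applies the word negligible only to events caused by the scan.

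**The concern.** The reporting windows suit a study of a tracer injection and a scan. This trial randomizes patients to a management strategy. The background section {6a} places the danger in what follows a doubtful image: "initial diagnostic uncertainty is common, which may lead to an increased risk of misdiagnoses and unnecessary interventions". Re-operation, a changed drug regimen and continued treatment or observation all come after the PET result, and so do their complications.

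If collection regardless of relatedness stops within days of the result, the published serious-event table will say little about the strategy. A reader who wants to set fewer unnecessary interventions against serious morbidity by arm would not find the second half of that comparison. Co-primary outcome 1 does not supply it. It counts whether an unnecessary intervention took place, not whether an intervention, necessary or not, led to a serious complication.

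**Working it through.** **Inputs.** From Table 1, counted from the index MRI result: randomization about Days 5 to 16, PET about Days 7 to 30, PET result about Days 10 to 33. From section {22}: 7 days for serious events and 30 days for related events, both starting at the scan in the PET arm and at randomization + 7 days in controls. Assumption: month 6 is Day 182 on the same clock.

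**Lag from scan to result.** Pairing the ends of the ranges: 10 − 7 = 3 days and 33 − 30 = 3 days.

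**PET arm, serious events.** The window ends on Day 7 + 7 = 14 or Day 30 + 7 = 37. Days left after the result: 14 − 10 = 4 and 37 − 33 = 4.

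**PET arm, related events.** The window ends on Day 7 + 30 = 37 or Day 30 + 30 = 60. Days left after the result: 37 − 10 = 27 and 60 − 33 = 27.

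**Share of the time from result to month 6.** That time is 182 − 10 = 172 days or 182 − 33 = 149 days.
- Serious events: 4/172 = 2.3% to 4/149 = 2.7%.
- Related events: 27/172 = 15.7% to 27/149 = 18.1%.

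**Control arm.** The windows open on Day 5 + 7 = 12 to Day 16 + 7 = 23. Serious-event collection ends on Days 19 to 30, related-event collection on Days 42 to 53.

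**Sensitivity to the lag.** The ranges are approximate and individual lags are not given. For a lag of L days, 7 − L days remain after the result: all 7 if the result comes on the day of the scan, none if it takes a week.

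**What else is recorded after the windows, in both arms.**
- Unnecessary interventions and final diagnosis: month 6.
- Survival status: month 6 and end of trial.
- QLQ-C30 and BN20: weeks 6 and 12, month 6.
- Healthcare consumption: month 6, with in- and out-patient care extracted from health records as cost data {18a}.

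**What is left out.** None of these items records a complication of biopsy or debulking, or an admission for treatment toxicity, as a harm. Debulking for mass reduction after a PET reading of recurrence may not meet the definition of an unnecessary intervention at all; a serious complication of it after the window would appear only indirectly, as cost or in a questionnaire score.

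**The case against.** The strongest reply is that the risks named in the background (misdiagnosis, delay, unnecessary surgery or treatment) are the trial's own endpoints. Co-primary outcome 1 counts diagnostic surgery and drug treatment given on a wrong presumed diagnosis in either direction. Survival, quality of life and healthcare consumption run to month 6 or later in both arms. This stands. A reader might infer that the trial measures benefit for 6 months and harm for one week, or that all harms of PET-guided management go unrecorded. The document does not support either reading.

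The 30-day window also counts for something. It reaches about 27 days past the result and includes events that staff observe. A reader might take it to cover tracer and scan harm only, but section {22} does not say what an event must be related to, and it applies the rule to controls, who have no study scan. What remains is that the rule depends on an undefined relatedness judgment. It cannot be relied on to pick up a surgical complication or drug toxicity.

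The adverse-event marks in Table 1 stop at the PET result column. That is not the end of collection, because footnote c extends it.

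The objectives include no safety objective, and treatment in both arms is standard of care. This makes the gap less serious but does not close it. Nor does it help that the article condenses a longer protocol: the windows and the publication rule are stated outright.

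**Conclusion.** The point holds in a limited form. Serious-event collection regardless of relatedness ends about 4 days after the PET result, 2.3 to 2.7% of the time from result to month 6. Related-event collection covers about 16 to 18% of that time, with relatedness left undefined. Non-fatal serious harms of the management that follows the result are therefore largely not recorded as harms in either arm. Deaths, unnecessary interventions, quality of life and healthcare consumption are captured.

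The figures rest on paired ends of approximate ranges and on month 6 as Day 182. The 4 days can be anything from 0 to 7 for a single patient. The document gives no rate for procedure complications or toxicity admissions, so the number of missed events cannot be estimated. The primary analysis is not affected. The loss is in what the trial can report about harm beside its main result.

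**What to change.** Keep the short scan-related windows as they are. Add to section {22} and Table 1 a non-expedited record, in both arms, from randomization to month 6 and regardless of relatedness, of:
- complications of biopsy or debulking;
- unplanned hospitalization, with its main reason;
- death.

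Take it from the health records already used at month 6 for unnecessary interventions, final diagnosis and healthcare consumption. Tabulate it by randomized arm beside co-primary outcome 1. Starting at randomization also gives a start date to patients in the PET arm who never have the scan.

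In sections {30} and {21a}, limit the negligible-risk wording to the scan; section {22} already does so.

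The cost is protocol wording, a few case report form fields and some extra chart extraction across the eight centers, with no added visits. Ascertainment will be unblinded and events from tumor progression will be common, so the table should be read as descriptive. Full retrospective CTCAE grading of all severe events over 6 months is not asked for: with unblinded staff, its yield against the work is debatable.

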**Fig. 1 Fig1:**
[figure not shown]
Study design flowchart. Potential number of patients, and number of patients meeting inclusion criteria, is based on real-life data from the included centers, very conservatively set at 50% of historical patient numbers 2019–2021. * Patients not receiving the intervention ([^18^F]FET PET) will be included in final analysis and not be replaced, according to an intention-to-treat design. Follow-up questionnaires will be administered if feasible. In this way, bias due to selective drop-out between arms will be avoided. ^#^Withdrawal of consent due to patient preference may occur, but is expected to be rare since patients have minimal extra burden during follow-up; transfer of care to a non-participating hospital is possible, but occurs only very infrequently in clinical practice. ^@^ The study features is a single-timepoint intervention (regular MRI, already available at baseline; versus [^18^F]FET PET), making discontinuation of the intervention during follow-up a non-relevant issue

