### Criteria for discontinuing or modifying allocated interventions {11b}

This study has a single time-point intervention, making discontinuation of the intervention during follow-up a non-relevant issue. When a participant in the intervention group does not undergo the [^18^F]FET PET scan, this can be due to worsened clinical condition (or death) or participant request.

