### Strategies to improve adherence to interventions {11c}

As the intervention is a single [^18^F]FET PET scan that is performed almost directly after randomization, no specific monitoring adherence procedures are applicable.

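### The SAE window opens at the PET scan in Arm A but at randomization + 7 days in Arm B, so Arm A patients who are never scanned have no SAE window

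*Protocol article*

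**What the plan says.** The collection rule is in the protocol article under Adverse event reporting and harms {22}. There are two windows. For SAEs: "All serious adverse events (SAEs) will be systematically reported for 7 days in both groups, regardless of relatedness". For other events: "These possibly/probably related AEs will be reported for 30 days in both groups". The start of both is given as: "Both time windows start from the date of the PET scan in the intervention group and 7 days after randomization in the control group". The section lists what it expects to see: "expected SAEs are hospitalization, persistent or significant disability or incapacity, or death due to glioblastoma progression". It adds that events meeting these criteria will appear in the trial publications.

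Three other places bear on the rule.

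- Criteria for discontinuing or modifying allocated interventions {11b} accepts that some Arm A patients will not be scanned and says that "this can be due to worsened clinical condition (or death) or participant request".
- The legend of Fig. 1 says that patients who do not receive the scan "will be included in final analysis and not be replaced, according to an intention-to-treat design".
- Table 1 places randomization at about days 5–16 and the scan at about days 7–30, both counted from the index MRI result. Strategies to improve adherence to interventions {11c} describes the scan as "performed almost directly after randomization".

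No start date is given for an Arm A patient who is never scanned.

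**The concern.** A window shown for both arms should open at a point that every randomized patient can reach in the same way. Here Arm B's window opens at a fixed time after randomization, and Arm A's opens at an event that itself depends on the patient's condition. Clinical worsening, one stated reason for missing the scan, is also what produces the expected SAEs. An Arm A patient who deteriorates before the scan and is then hospitalized is not recorded. A control with the same course, alive at day 7 and hospitalized in the following week, is.

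At stake is the SAE table by arm in an open-label trial. This is a rule about what is collected, so SAEs that were never recorded cannot be restored by a later choice of analysis.

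**Working it through.** The article gives no SAE rate and no figure on this point to reproduce. The check is a reading of the rule followed by illustrative arithmetic.

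**Step 1. Who has a window?**

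| Patient | SAE window as written |
|---|---|
| Arm B, alive at randomization + 7 days | days 7 to 14 after randomization |
| Arm A, scanned on day *d* after randomization | days *d* to *d* + 7 |
| Arm A, never scanned | none defined |
| Arm B, dies before day 7 | none |

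The third row is the defect. The fourth shows that the first week is uncounted in Arm B too.

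**Step 2. Size of the selection effect.** From the article: 72 patients per arm. Assumed: no true effect of PET on SAEs; a 7-day SAE risk of 5% in patients fit to be scanned; an unscanned share *u* of 5%, 10% or 15%; a 7-day SAE risk *r* of 20% to 60% in the patients who would go unscanned; the same mix of patients in Arm B, all alive at day 7.

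- Arm A expected patients with an SAE = 72 × (1 − *u*) × 0.05
- Arm B expected patients with an SAE = 72 × [*u* × *r* + (1 − *u*) × 0.05]
- Difference = 72 × *u* × *r*

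| *u* | Arm A | Arm B, *r* = 20% | Arm B, *r* = 60% | Difference |
|---|---|---|---|---|
| 5% | 3.4 | 4.1 | 5.6 | 0.7 to 2.2 |
| 10% | 3.2 | 4.7 | 7.6 | 1.4 to 4.3 |
| 15% | 3.1 | 5.2 | 9.5 | 2.2 to 6.5 |

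If patients miss the scan only by request and carry the ordinary 5% risk, the difference is 72 × *u* × 0.05, or 0.2 to 0.5 patients. At *u* = 10% that is 3.2 against 3.6.

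**Step 3. Timing in scanned patients.** Pairing like with like in Table 1, the scan falls 7 − 5 = 2 days (earliest with earliest) to 30 − 16 = 14 days (latest with latest) after randomization. A scan on day 2 gives an Arm A window of days 2–9; a scan on day 14 gives days 14–21. The control window is days 7–14.

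Assume a daily SAE hazard of 0.05/7 at randomization that rises 2% per day. The 7-day risk from day *s* is 1 − exp(−*H*), with *H* = (0.05/7)/0.02 × [exp(0.02(*s* + 7)) − exp(0.02 *s*)].

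- *s* = 2: *H* = 0.0559, risk 5.4%
- *s* = 7: *H* = 0.0617, risk 6.0% (Arm B)
- *s* = 14: *H* = 0.0710, risk 6.9%

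An early scan therefore lowers the Arm A figure relative to Arm B, and a late scan raises it. With a constant hazard the timing makes no difference.

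**The case against.** The other side has a good deal on its side.

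- **No safety test is planned.** The section promises only that events will be published. Safety is not a listed outcome and the statistical methods contain no safety test. This stands: the issue is the accuracy of a descriptive table.
- **The 7-day offset mirrors the expected scan time.** Seven days lies within the 2 to 14 days derived from Table 1, so for scanned patients the windows are roughly aligned. This stands, but it does nothing for the unscanned.
- **Important outcomes are captured elsewhere.** Overall survival runs from the index MRI result in both arms, so deaths are counted by arm. Healthcare consumption is collected at month 6. The 30-day window covers only possibly or probably related events, and an unscanned patient has no scan-related event to miss. This stands, and it confines the point to the 7-day all-cause SAE record.
- **A substitute start date may be in the full protocol.** It may, but the article states the start rule for both arms without exception, and followed as stated that rule leaves these patients out.

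A reader might go further in three ways that the article does not support.

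- **That the comparison favors PET.** Selection tends that way, but late scans can work against PET, and the first week after randomization is uncounted in Arm B as well.
- **That the windows may lie 25 days apart.** That figure pairs the earliest randomization with the latest scan (30 − 5), across ranges that are marked approximate.
- **That about 7 of 72 Arm A patients (10%), the sickest, would be lost.** The sentence that begins "In case more than 10% of the patients in the intervention arm do not undergo the [^18^F]FET PET scan" sets a trigger for an additional per-protocol analysis. It is neither a forecast nor a tolerated rate, and participant request is also a stated reason for missing the scan.

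**Conclusion.** The point holds in a limited form. The stated rule gives the two arms different starts and leaves unscanned Arm A patients without an SAE window, although they stay in the trial by intention to treat. Because the window counts SAEs of any cause and the expected ones come from tumor progression, the selection tends to lower the Arm A count.

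Under the assumptions in the working, the shortfall is about 1 to 6 patients with an SAE in Arm A, and under one if the unscanned carry ordinary risk. The unscanned shares and SAE risks are assumptions, so this range shows scale and is not an estimate. The net direction is uncertain once scan timing is added. The timing illustration also ignores that patients who reach a late scan have stayed well enough to have it.

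No primary or secondary efficacy result is affected. The rule is still worth changing now: recruitment is estimated to run to December 2027, and unrecorded SAEs cannot be recovered afterwards.

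**What to change.** For SAEs reported by arm, define one randomization-based start and the same window length in both arms, whether or not the scan is done, and report by randomized arm. Randomization + 7 days, as already used in Arm B, would serve. With that start, every patient alive at day 7 has a window, and the expected difference is zero if PET has no effect on SAEs. At minimum, give unscanned Arm A patients that start date; this closes the gap in Step 1 but leaves the timing difference in Step 3.

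Keep the PET-anchored windows as an additional Arm A listing of scan-related events, since a scan on day 14 or later would otherwise fall at or beyond the end of the common window.

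The cost is a change of wording and modestly more SAE reporting in Arm A: at most 7 extra days per patient where the two windows do not overlap, or 72 × 7 = 504 patient-days as an upper limit. Arm B reporting is unchanged. Patients already recruited in Arm A, including any who were not scanned, would need their records checked for the common window.
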